### Interventions

#### SPARX-R

The experimental intervention in this trial is SPARX-R, a revised version of SPARX, which was originally developed using an unguided, interactive fantasy game format that provides CBT skills to treat mild to moderate symptoms of depression in help-seeking adolescents. SPARX resulted in a decline in symptoms of depression and was shown to be non-inferior to treatment as usual, which consisted primarily of face-to-face therapy with a counsellor, general practitioner or clinical psychologist [36]. In this trial, response rates and treatment satisfaction did not differ between groups, nor did symptoms of depression, anxiety, hopelessness or quality of life, at post-intervention and 3-month follow-up. Further, remission rates were higher in the SPARX group. A pragmatic randomised controlled trial in a group of young people excluded from mainstream education also found SPARX to be superior to waitlist control with regard to reducing symptoms of depression [60]. Attitudes towards SPARX have been predominantly positive, with youth workers in New Zealand, young people alienated from mainstream schooling and rural Australian youth endorsing the program as a viable alternative to traditional therapeutic interventions [61–63]. Indeed, students in alternative education felt that SPARX should be offered to all adolescents in courses like their own, as they felt that providing the intervention at an indicated or targeted level might be stigmatising and that all could benefit from the lessons provided [64].

SPARX-R uses the same content as SPARX but is framed as a preventive intervention. For example, in the original version, participants are told that ‘*SPARX was made to help young people who feel down or depressed*’. In contrast, the SPARX-R introduction informs participants that ‘*this version of SPARX was made to help young people who are having hassles and feeling down, stressed or angry a lot of the time. Even if you are doing fine, SPARX-R can help strengthen your skills for dealing with problems when they do come along*’. Participants using SPARX-R choose and personalise an avatar and are led through the program by a virtual guide character who provides context and instruction and relates the content of the program to the participant’s real-life experiences. The participant navigates through a series of challenges and obstacles within a fantasy world that has been overrun by gloomy, negative, automatic thoughts. The student’s mission is to restore balance in the game world. The program has seven modules (levels), each of which takes approximately 20–30 minutes to complete. The modules cover the following topics: (1) finding hope, (2) being active, (3) dealing with strong emotions, (4) overcoming problems, (5) recognising unhelpful thoughts, (6) challenging unhelpful thoughts and (7) bringing it all together. SPARX-R will be delivered to participants via the internet on desktop computers in school classrooms.

#### lifeSTYLE

lifeSTYLE is an adaptation of an interactive, online program that was originally developed as a control intervention for a previous trial targeting adults with suicidal thoughts [65]. The format and structure of the program have been retained, but the content has been adapted to suit the needs of a younger group. The aim of the intervention is to provide an engaging and useful resource for young people that matches the intervention in terms of duration and attention but without providing any strategies or techniques to prevent or manage mental health difficulties. The program also includes seven modules (approximately 25 minutes each) and covers the following topics: (1) independence, (2) participating in your community, (3) work skills, (4) mobile phone safety and hygiene, (5) healthy skin, (6) sustainable eating and (7) maintaining a healthy home environment. Each module includes information about the specified topic as well as interactive activities such as quizzes, myth busters, videos and scenarios that students can reflect on and respond to. As with SPARX-R, the intervention is delivered to students in school classrooms via the online platform on desktop computers.

### Procedures

Immediately before the baseline assessment, during an allocated class period, school teachers will provide students with a URL that will take them to the trial registration page. Students will use their unique identification code to register at this page and set up a personal password. Students will also be required to provide a personal email address and mobile telephone number so that they can be contacted during the follow-up period after they have left school.

Students with parental and personal consent will complete questionnaires on three occasions during class time (pre-intervention, post-intervention and 6-month follow-up), as well as an additional 18-month follow-up questionnaire once they have graduated from secondary school. The timing of assessments was designed such that the 6-month follow-up will be conducted just before the trial HSC examination period, one of two major examination periods during the final year of school.

All assessments will be conducted via the online platform. Teachers will direct students to log on to the platform during the first three assessments, and participants will be emailed a link to log on directly from their personal computer on the final assessment occasion. All students will complete their allocated intervention (SPARX-R or lifeSTYLE) over the course of approximately 5–7 weeks in school via the online platform. Schools will timetable the intervention sessions to fit in with their respective schedules, but they will be advised to space sessions out so that students have sufficient time to reflect on the material presented in each module. On each assessment occasion, students who do not complete their assessments during the scheduled class time (owing to absence or other conflicting duties) will be asked to complete the questionnaires in their own time. A reminder email will be sent 1 week after the scheduled assessment, and a final reminder will be sent another week later to any student who still has not completed the scheduled assessment. Trial researchers will monitor completion of assessments and will remain in close contact with participating schools to ensure that school staff encourage assessment and intervention completion by all participating students. Students will no longer be able to access or complete assessments 1 month after their school’s scheduled assessment date.

### Measures

The administration schedule for each of the assessment measures described below is provided in Table 2.

**Table 2 Tab2:** Assessment administration schedule

Assessment	Construct	Baseline	Post-intervention	6 months	18 months	Other
Primary outcome						
MDI	Depression symptoms	X	X	X	X	
Secondary outcomes						
ATAR	Academic performance					Collected via schools after final examination results are released
SCAS	Anxiety symptoms	X	X	X	X	
YRBS	Suicidal ideation	X	X	X	X	
DSS-P	Personal stigma	X	X	X	X	
Predictor variables						
SSSS	Social support	X				
PMS	Mastery	X	X	X		
RRS	Rumination	X	X	X		
PID-5-BF	Personality traits	X				
HPLS-Brief	Hopelessness	X				
INQ	Belongingness/burdensomeness	X				
ACSS	Capability	X				
ISI	Sleep disturbance	X				
MEQr	Sleep–wake patterns	X				
PS/PC	Expressed emotion	X				
Cost-effectiveness variables						
TiC-P	Service use			X	X	
Questionnaire	Days out of role			X	X	
AQoL	Quality of life			X	X	
Process variables						
Questionnaire	Expectation of success	X				
Intervention data	Adherence					Collected automatically via SPARX-R and lifeSTYLE
Questionnaire	Acceptability, usability		X			
IIAM	Reasons for dropout		X			
Parent outcomes						
PHQ-9	Depression	X		X		
GAD-7	Anxiety	X		X		

*ACSS* Acquired Capability for Suicide Scale; *AQoL* Assessment of Quality of Life; *ATAR* Australian Tertiary Admission Rank; *DSS-P* Depression Stigma Scale–Personal Stigma subscale; *GAD-7* Generalized Anxiety Disorder 7-item scale; *HPLS* Hopelessness Scale for Children; *IIAM* Internet Intervention Adherence Measure; *INQ* Interpersonal Needs Questionnaire; *ISI* Insomnia Severity Index; *MDI* Major Depression Inventory; *MEQr*  Reduced version of the Morningness Eveningness Questionnaire *PS/PC* Perceived Sensitivity/Perceived Criticism scale; *PHQ-9* Patient Health Questionnaire-9; *PID-5-BF* Personality Inventory for DSM-5; Brief Form; *PMS* Pearlin Mastery Scale; *RRS* Ruminative Response Scale; *SCAS* Spence Children’s Anxiety Scale; *SSSS* Schuster Social Support Scale; *TiC-P* Trimbos/iMTA questionnaire for Costs associated with Psychiatric illness; *YRBS* Youth Risk Behavior Survey

### Primary outcome measure

#### Major Depression Inventory

The Major Depression Inventory is a 12-item self-report measure of depressive symptoms [66]. The items of the MDI evaluate the presence and duration of depressive symptoms according to criteria of both the International Classification of Diseases, 10th revision (ICD-10), and the *Diagnostic and Statistical Manual of Mental Disorders, Fourth Edition* (DSM-IV) [67]. Participants rate the degree to which they have experienced each of the 10 symptoms over the preceding 2 weeks on a 6-point scale, ranging from 0 (at no time) to 5 (all of the time). The MDI has acceptable sensitivity and specificity for the diagnosis of depression according to the ICD-10 and DSM-IV [66]. To accord with DSM criteria and evaluate functional impairment, we included an extra question on the MDI asking participants to indicate (on the same scale) the degree to which their depressive symptoms interfered with activities of daily living over the previous 2-week period.

### Secondary outcome measures

#### Screen for lifetime presence of a major depressive episode or manic episode

Screening questions from the Structured Clinical Interview for DSM-IV disorders–Mood module [68] were included to provide an indication of a lifetime presence of a major depressive episode or manic episode. Mood, anhedonia, mania and irritability are assessed, and participants respond by answering ‘yes’ or ‘no’ to whether they have ever had prolonged experiences of each symptom (2 weeks for mood and anhedonia, 1 week for mania and irritability).

#### Australian Tertiary Admission Rank

Participants’ academic performance will be assessed by means of their estimated Australian Tertiary Admission Rank (ATAR) scores. With students’ consent, schools will provide researchers with students’ HSC results, from which an estimate of each student’s ATAR score will be calculated using a standard online ATAR calculator.

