### Hypotheses

With regard to the primary outcome measure, we predict that, relative to participants in the attention control condition, students who are assigned to the SPARX-R condition will demonstrate lower levels of depressive symptoms immediately following the intervention. We also anticipate that depressive symptoms for SPARX-R participants will be lower than those in the lifeSTYLE group at 6- and 18-month follow-up. For secondary outcomes, we expect that, relative to the lifeSTYLE group, participants in the SPARX-R group will perform significantly better in their HSC and demonstrate reduced anxiety, suicidal ideation and/or behaviour and stigma following the intervention and at follow-up. We anticipate that SPARX-R will have an effect on the parents of students allocated to this group, reducing their own symptom levels at 6 months, relative to parents of students in the attention control group. Finally, we predict that SPARX-R will be more cost-effective than lifeSTYLE, owing to fewer days out of role (e.g., studying, working), better quality of life and less use of health services at 6- and 18-month follow-up.

For those in the SPARX-R group, we predict that a positive response to the prevention program will be associated with the following variables at baseline: absence of family history of depression, high social support, high mastery, low rumination, low neuroticism and/or negative affect, low hopelessness, low thwarted belongingness, low burdensomeness, low sleep disturbance, unimpaired sleep–wake patterns, low expressed emotion, low cortisol levels and lack of genetic vulnerability factors.

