### Setting

The trial will be conducted in government, independent and Catholic secondary schools in New South Wales, Australia. Government schools in New South Wales are classified as either comprehensive or selective. Comprehensive schools accept enrolments of all students in the surrounding area, whereas selective high schools use an entry examination to enrol students with superior academic ability. The first stage of the trial will be conducted in government schools in metropolitan Sydney. Ethical approval to collect biological data in government schools was not granted. Therefore, measures of cortisol and genetic vulnerability will be collected only in the 2016 cohort (which we expect will comprise primarily independent and Catholic schools), pending ethical approval.

The 2015 cohort will comprise students from selective government secondary schools. Although study-related stress is a widely experienced phenomenon, academically gifted students may be particularly at risk of experiencing stress-related mental health difficulties during the final examination period, given the high rates of perfectionism in this group, as well as the pressure to succeed from parents, schools, the media and students themselves (see, e.g., [47]). Perfectionism has been shown to be a strong predictor of prospective stress in the context of an academically demanding end-of-semester period [48]. Further, the increased academic workload and considerable number of hours spent studying by students in a demanding education program is likely to compound this pressure and act as an additional source of stress [49]. Indeed, high-stakes examinations can lead to a range of negative outcomes in high-achieving students, including anxiety, depression, school absence, helplessness and ulcer [21, 50]. Thus, the characteristics of students in selective high schools make these schools a particularly relevant target for the present trial. It should be noted that some government schools have both selective and comprehensive streams. All students at these partially selective high schools will be eligible to participate; however, streaming status will be recorded, and school type will be accounted for in analyses.

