### Randomisation

Each participating school (cluster) will be randomised to complete the SPARX-R or lifeSTYLE program. School-level randomisation will be used to avoid contamination between conditions, for the ecological validity of providing the intervention at the cluster level and for practical convenience. A statistician not involved in the implementation of the trial will randomly allocate schools using the allocation sequence outlined below. The identity of schools will be concealed from the statistician during this process.

Randomisation in cluster randomised trials is problematic because the number of clusters involved is usually relatively small. In large, individually randomised trials, balance in the makeup of each arm is achieved as a function of the numbers involved. Balance between arms can be achieved by stratification or minimisation [57]. Stratification can accommodate only a limited number of balancing variables, and minimisation is based on incremental assignment of participants to groups. In TriPoD, the number of potentially relevant variables to be balanced between arms is quite large (e.g., sex, number of enrolled students, Index of Community Socio-Educational Advantage school index, language background other than English), and all available sites will be enumerated before commencement of the trial. Achieving approximately equal numbers of participants in each arm is also an aim of the allocation design, as this will determine the study’s power in the absence of substantial clustering effects. Accordingly, this attribute of each school will be used not to estimate the degree of balance, but rather to screen potential grouping after balanced combinations have been selected.

We will use the method developed and implemented by Carter and Hood [58] to ensure balance between intervention arms. This enumerates all possible divisions of the available schools into two groups and calculates a balance index [59] for each of these groupings. The 10 most balanced groupings will be retained after excluding any grouping resulting in a deviation of more than 10 % in predicted individual participant sample size between inventions. The allocation schedule will be selected at random from the groupings retained.

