### Analysis

Primary analyses will be undertaken on an intention to treat basis, including all participants as randomised, regardless of treatment actually received. Effectiveness of SPARX-R will be established using a planned contrast of change from pre-test to the post-intervention in the active compared with placebo condition on the MDI within a mixed-effects model repeated-measures analysis [104]. School will be included in analyses as a random effect to evaluate and accommodate clustering effects. Variables used in determining allocation balance will be evaluated and retained in analyses where they are significant or quasi-significant. An unconstrained variance–covariance matrix will model within-individual dependencies. Transformation of scores, including categorisation, may be undertaken to meet distributional assumptions and accommodate outliers. Contrasts comparing change on the MDI from pre-test to other occasions of measurement will be undertaken as secondary analyses.

Models for binary outcomes analogous to the primary analysis approach will be used to compare the prevalence rates (MDD status) and other dichotomous outcomes between the two treatment arms at the endpoint and other occasions of measurement. Relative and absolute risk reduction, NNT (see [105]) and other relevant indices will be calculated for these outcomes and undertaken separately for participants who did not meet criteria for caseness at pre-test to assess the effect of the intervention on incidence. In analyses of scaled secondary variables, we will use methods comparable to those of the primary analysis. Subsidiary complier and related analyses will estimate the efficacy of SPARX-R in participants who completed modules from the SPARX-R program to produce a clinical impact (estimated to be four or more modules) [36]. In exploratory analyses, we will examine the effects of moderators and mediators of treatment (see [106]).

Interim analysis of outcomes of the 2015 cohort will be undertaken following the methods described above. Although the sample available will be of limited size, the outcome of this analysis will be used to guide the second stage of the trial, planned for 2016. Should there be clear evidence of lack of effect, based point estimates of effectiveness and associated confidence intervals, consideration may be given to abandoning second-stage recruitment or seeking possible modifications of the intervention.

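### The HSC hypothesis rests on one post-examination ATAR with no prior-attainment measure, so no change contrast can be formed and precision is likely to be poor if attainment clusters by school

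*Protocol article*

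**What the plan says.** - **Hypothesis.** The Hypotheses section expects that "participants in the SPARX-R group will perform significantly better in their HSC" than the lifeSTYLE group. Table 1 lists academic performance among the key secondary outcomes.
- **Measure.** The section on the Australian Tertiary Admission Rank states: "Participants’ academic performance will be assessed by means of their estimated Australian Tertiary Admission Rank (ATAR) scores". Table 2 gives the timing as "Collected via schools after final examination results are released". No academic measure is marked at baseline or at any other occasion.
- **Analysis.** The primary analysis contrasts the arms on pre-to-post change in the MDI within a mixed model with a random school effect. For the rest: "In analyses of scaled secondary variables, we will use methods comparable to those of the primary analysis". Variables used for allocation balance stay in the model if significant or nearly so.
- **Allocation.** "Each participating school (cluster) will be randomised to complete the SPARX-R or lifeSTYLE program". The Randomisation section notes that "the number of potentially relevant variables to be balanced between arms is quite large". Its examples are sex, enrolment, a socio-educational index and language background. The allocation is drawn from the ten most balanced groupings.
- **Schools.** The Setting section explains that "selective high schools use an entry examination to enrol students with superior academic ability" and promises that school type will be accounted for. Under Trial status, the 2015 cohort is eight selective and two partially selective schools. The 2016 cohort is expected to be mainly independent and Catholic schools.

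**The concern.** A change contrast does two jobs in this design: it removes stable differences between students, and it removes stable differences between schools. For the ATAR neither is available, because there is nothing to subtract or adjust for. Differences in attainment between schools that exist before the trial therefore stay in the error term, except for the part captured by school type or a retained balance variable.

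This matters more for the ATAR than for the symptom scales, because some participating schools admit students on academic ability. The sample size section plans only for the MDI, with an ICC of 0.02 and a baseline correlation of 0.5. Neither assumption carries over to an academic outcome without a baseline. At stake is whether a stated hypothesis can be answered with useful precision, and whether a null or surprising HSC result could be told apart from chance imbalance between two sets of about 15 schools.

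**Working it through.** **The plan's own figure.** For an effect of 0.20 SD, 80% power and two-sided 5%, a t-based calculation gives 393.4 per arm, rounded up to 394. The design effect is 1 + (25 − 1) × 0.02 = 1.48, and 2 × 394 × 1.48 = 1166, as stated. This corresponds to a change score: with r = 0.5 its variance is 2(1 − 0.5) = 1. The figure concerns the MDI only; the protocol gives no ICC, effect size or power for the ATAR.

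**Inputs for the ATAR.**
- From the Sample size section: 30 schools, taken as k = 15 per arm; about m = 50 students per school; 80% power; two-sided 5%.
- Assumed: ICC for attainment of 0.02 (the only ICC in the document, there for the primary outcome), 0.1, 0.2 or 0.3.
- Assumed: a school-level prior-results covariate explains a share R² of 0.5 or 0.8 of the between-school variance.
- Equal school sizes; no gain yet credited to school type or balance variables.

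**Formula.** In total-SD units, Var(difference) = 2[ICC(1 − R²) + (1 − ICC)/m]/k. The detectable difference solves noncentral-t power = 0.80 with 28 degrees of freedom, or 27 with the covariate. It is about 2.90 standard errors with 28 and 2.91 with 27.

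**Example, ICC 0.1, no covariate.** 2 × (0.1 + 0.9/50)/15 = 0.01573; the standard error is 0.125; 2.90 × 0.125 = 0.36 SD.

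**Example, ICC 0.1, R² = 0.8.** 2 × (0.02 + 0.018)/15 = 0.00507; the standard error is 0.071; 2.91 × 0.071 = 0.21 SD.

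| Assumed ICC | No covariate | R² = 0.5 | R² = 0.8 |
|---|---|---|---|
| 0.02 | 0.21 | 0.18 | 0.16 |
| 0.1 | 0.36 | 0.28 | 0.21 |
| 0.2 | 0.49 | 0.36 | 0.25 |
| 0.3 | 0.59 | 0.43 | 0.29 |

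**Power for 0.20 SD.** This is the planning effect for the MDI, used here only as a yardstick. With no covariate, power is about 76%, 34%, 21% and 16% at the four ICCs. With R² = 0.8 it is 77%, 61% and 49% at ICC 0.1, 0.2 and 0.3.

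**Chance difference from schools alone.** Its standard deviation is √(2 × ICC/15): 0.05, 0.12, 0.16 and 0.20 SD at the four ICCs.

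**Sensitivity.** With 40 students per school (20% loss), the no-covariate column becomes 0.22, 0.37, 0.50 and 0.60. School-level variance dominates, so the number of students per school matters little.

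**The case against.** Five points can be made for the plan.

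1. **The comparison is not raw.** There is a random school effect, school type is accounted for, allocation comes from the most balanced groupings, and balance variables, including a socio-educational index, may be retained. This stands. The no-covariate column is therefore a starting point, and some of the gain shown may already be achieved by what is planned. School type cannot, however, separate the eight fully selective schools of 2015 from each other.
2. **Staging helps.** All 2015 schools are selective or partly so, and independent and Catholic schools are expected mainly in 2016, so the coarsest contrast in ability lies largely between stages. This also stands, and it lowers the ICC that remains after school-type adjustment.
3. **The wording is comparable methods, not identical ones.** An endpoint mixed model with a school effect fits that wording, and an analysis plan could specify it. This is fair as to the model. But no analysis plan can adjust for prior attainment unless someone obtains it, and the protocol plans no such data.
4. **The list of balance variables gives examples only.** Prior attainment is not ruled out, but it is not named either.
5. **The ATAR is one of several secondary outcomes, and the trial is sized for the MDI.** True, and this limits the weight of the point.

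A reader might infer that school differences will swamp any program effect, or that the hypothesis cannot be answered at all. The documents do not show this: they give no ICC or effect size for the ATAR, and at an ICC of 0.02 the detectable difference is about 0.21 SD. A reader might also infer bias. Randomisation with a school random effect rules out a systematic tilt; what remains is imprecision and chance imbalance.

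**Conclusion.** The point holds as one of fit and precision. The primary-style change contrast does not exist for an outcome measured once, and no prior-attainment variable is named for balance or adjustment. The planned comparison is valid, but likely to be imprecise if attainment clusters by school: before any gain from the adjustment already planned, about 0.36 SD is detectable at ICC 0.1, 0.49 at 0.2 and 0.59 at 0.3, against 0.21 at 0.02. A school-level covariate explaining 50–80% of between-school variance would bring the first three to 0.28–0.21, 0.36–0.25 and 0.43–0.29 SD.

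Both the attainment ICC and the share explained are assumptions. That clustering exceeds 0.02 is plausible where schools select on ability, but the documents do not establish it.

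**What to change.** - When HSC results are collected from schools (in 2016 for the 2015 cohort), also obtain each school's mean HSC result, or mean estimated ATAR, for the Year 12 cohort preceding the trial cohort.
- Specify the ATAR analysis as an endpoint mixed model with a random school effect, and state that it is not a change contrast. Enter the school's prior mean and school type or stream status as fixed covariates, exempt from the rule that retains variables by significance.
- Add the prior mean to the balancing variables for the 2016 schools. This cannot help the ten schools already allocated, for which covariate adjustment has to serve.

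The cost is one small data request per school, one school-level degree of freedom for the prior mean, and a few lines of analysis text. An individual Year 11 baseline is not proposed: it would exist for the 2016 cohort only, would need new consent, and is not shown to share a common scale across schools.
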